### Outcome measures

Clinical and anthropometric parameters (weight, height, waist circumference and blood pressure) will be recorded. A hepatic ultrasound (US) test will also be performed at the beginning of the two intervention periods, as well as at the end of the intervention periods. US diagnostic criteria for diagnosis and grading of hepatic steatosis will be used [16]. Smoking habits and anxiolytic and antihistaminic drug intake will also be recorded.

Blood samples will be collected after 12 h of fasting at the beginning and at the end of each intervention period (t0, t12, t18 and t30). Stool samples will also be taken at baseline and at 6, 12, 18, 24, and 30 weeks (t0, t6, t12, t18, t24, and t30, respectively). Serum will be collected by centrifugation of blood samples for the determination of biochemical and inflammation biomarkers. Faecal samples will be collected and kept at − 80 °C until analysis. All samples will remain frozen at − 80 °C in the BSSPA Platform.

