**Methods/design:**

We describe a randomized, double-blind, crossover, placebo-controlled, and single-centre trial. Sixty participants (aged 18 to 65 years) diagnosed with IRS will be randomized in a 1:1 ratio to receive either a daily dose of placebo or 5 × 10^9^ colony-forming units of *L. reuteri* V3401. The study will consist of two intervention periods of 12 weeks separated by a washout period of 6 weeks and preceded by another washout period of 2 weeks. The primary outcome will be the change in plasma lipopolysaccharide (LPS) levels at 12 weeks. Secondary outcomes will include anthropometric parameters, lipid profile, glucose metabolism, microbiota composition, hepatic steatosis, and inflammatory and cardiovascular biomarkers. Blood and stool samples will be collected at baseline, at the midpoint (only stool samples) and immediately after each intervention period. Luminex technology will be used to measure interleukins. For statistical analysis, a mixed ANOVA model will be employed to calculate changes in the outcome variables.

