### Randomization, allocation, and blinding

Patients will be randomly allocated in a 1:1 ratio to receive a capsule containing either lyophilized *L. reuteri* V3401 or placebo once daily with food for 12 weeks. A stratified block-randomization method of a software program for sequence generation will be used. After a 6-week washout, participants will crossover to receive the alternative intervention for another 12 weeks. Subjects and investigators will be blinded to the treatment allocation during the course of the intervention. The blind will be broken following consultation with the sponsor.

The capsules will be prepared in special containers with the random number label. Capsules will be delivered at the beginning of each intervention and six weeks later to ensure probiotic viability.

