### Intervention

We will conduct a standard semi-structured clinical interview with clinical assessment. Subsequently, we will audit the clinical reports to extract relevant information (Additional file 2). In addition, a physical examination, and a complete blood test will be also conducted prior to inclusion in the study. Participants meeting the inclusion criteria will be randomly assigned to the probiotic or placebo group. During the intervention, participants will be asked to ingest a capsule per day with food. Capsules will be administered over two periods of 12 weeks. During the washout period, participants will not receive dietary recommendations. Clinical follow-up visits will be scheduled at the beginning, midpoint, and end of each interventional period. At each visit, anthropometric parameters will be registered, and possible adverse effects will be recorded (Table 1).

**Table 1 Tab1:** Detailed study procedures

Visits (V) Week (W)			V1 (W-2)	V2 (W0)	V3 (W6)	V4 (W12)	Washout	V5 (W18)	V6 (W24)	V7 (W30)
Screening analysis			X							
Demographics/ general information			X							
Informed content form			X							
Randomization and allocation			X							
Treatment distribution			X							
Blood test				X		X		X		X
Stools collection				X	X	X		X	X	X
Hepatic ultrasound				X		X				X
Assessments	General outcomes									
		Clinical interview		X	X	X		X	X	X
		Blood pressure and anthropometry		X	X	X		X	X	X
		3-day dietary record		X		X		X		X
		Food Frequency Questionnaire (FFQ)		X		X		X		X
		Physical activity questionnaire (IPAQ)		X		X		X		X
	Primary outcomes									
		Plasma LPS		X		X		X		X
	Secondary outcomes									
		Blood Pressure		X	X	X		X	X	X
		HOMA		X		X		X		X
		Lipid profile		X		X		X		X
		Inflammatory markers		X		X		X		X
		Hepatic steatosis markers		X		X		X		X

The data and samples will be collected in the Complejo Hospitalario de Jaén by qualified personal, and will be codified according to the biobank of the Public Health System of Andalusia (BSSPA) guidelines. All samples will be managed and processed in accordance with BSSPA protocols. All samples will be centralized at the BSSPA facilities.

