### Dietary and physical activity control

Participants will be provided with a list of local foods to avoid due to their potential probiotic or prebiotic content. Subjects will be asked to complete a three-day dietary record at the beginning, midpoint, and end of each intervention period. Energy and dietary intakes will be assessed from the 3-day records using the EvalFINUT software (http://www.finut.org/evalfinut/). Additionally, subjects will complete the Food Frequency Questionnaire (FFQ) at the beginning of each intervention period. Participants will receive nutritional counselling on a healthy Mediterranean diet providing approximately 25 kcal/kg/ day to achieve and maintain 7% loss of initial body weight and increase moderate-intensity physical activity (such as brisk walking) for at least 150 min/week following the guidelines of the American Diabetes Association for the prevention or delay of DM2 [15]. Likewise, physical activity will be monitored through the International Physical Activity Questionnaire (IPAQ) at the beginning, midpoint, and end of each intervention period. In the following visits, an intensive lifestyle intervention programme will be carried out to reinforce the behaviour.

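### Table 1 leaves out the week-18 hepatic ultrasound that the text calls for; if the table is followed, ultrasound-graded steatosis has no starting value for period 2

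*Protocol article*

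**What the plan says.** The Outcome measures section of the protocol article states that a "hepatic ultrasound (US) test will also be performed at the beginning of the two intervention periods, as well as at the end" of those periods. It adds that ultrasound is used to diagnose and grade steatosis. The Abstract lists steatosis among the secondary outcomes: "Secondary outcomes will include anthropometric parameters, lipid profile, glucose metabolism, microbiota composition, hepatic steatosis, and inflammatory and cardiovascular biomarkers".

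The timing of period 2 follows from the section on randomization, allocation and blinding: "After a 6-week washout, participants will crossover to receive the alternative intervention for another 12 weeks". The blood-sampling sentence in Outcome measures gives the week labels, with samples taken "at the beginning and at the end of each intervention period (t0, t12, t18 and t30").

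Table 1, in the Intervention section, has a row "Hepatic ultrasound" with marks at V2 (W0), V4 (W12) and V7 (W30). The cell for V5 (W18) is empty.

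The section on dietary and physical activity control says: "Subjects will be asked to complete a three-day dietary record at the beginning, midpoint, and end of each intervention period". It sets the same three time points for the physical activity questionnaire (IPAQ). Table 1 marks both at W0, W12, W18 and W30, with nothing at W6 or W24.

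**The concern.** The text and the visit table give different schedules for the same assessment, and the scan on which they differ is the one that opens period 2. In a two-period crossover, the value at the start of period 2 does two jobs. It is the reference for the change during that period, and it shows whether the measure returned to its starting level after the washout. A team working from the table would collect neither piece of information for ultrasound grade, and a scan that was not done at week 18 cannot be recovered later.

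The gap also invites a poor substitute. With no week-18 scan, the nearest earlier one is at week 12, and an analyst who wants a period-2 change may reach for it.

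**Working it through.** The protocol gives no figure to reproduce here, so the check sets the two schedules side by side.

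**Start of period 2.** 12 weeks of treatment + 6 weeks of washout = week 18. This agrees with the t18 label for blood samples and with V5 in Table 1.

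**Is the empty cell real?** The table was extracted from PDF, so a shifted column had to be ruled out. The ultrasound row has 11 cells, the same as the header row. Other rows read in the same way fall where the text puts them: blood tests at W0, W12, W18 and W30, and stool samples at W0, W6, W12, W18, W24 and W30. The columns are aligned and the W18 ultrasound cell is empty.

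**Comparison of schedules.**

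| Assessment | Text | Table 1 | Difference |
|---|---|---|---|
| Hepatic ultrasound | W0, W12, W18, W30 | W0, W12, W30 | W18 missing from table |
| 3-day dietary record | W0, W6, W12, W18, W24, W30 | W0, W12, W18, W30 | W6, W24 missing from table |
| IPAQ | W0, W6, W12, W18, W24, W30 | W0, W12, W18, W30 | W6, W24 missing from table |
| Blood tests | W0, W12, W18, W30 | W0, W12, W18, W30 | none |

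**What each ultrasound schedule supports, per participant.**

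- Text: 4 scans and 2 within-period changes (W12 − W0 and W30 − W18).
- Table 1: 3 scans and 1 within-period change (W12 − W0).
- With 60 participants and no dropout, that is 60 × 2 = 120 within-period changes under the text and 60 × 1 = 60 under Table 1.

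**What the planned analysis needs.** The Statistical analysis section plans a repeated-measures model comparing values at the start, middle and finish of each period. Neither schedule has a midpoint scan, so for ultrasound the comparison reduces to start against finish. Under Table 1 that can be done in period 1 only.

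**Why week 12 does not stand in for week 18.** The week-12 scan is taken at the end of period-1 treatment and before the washout. A difference W30 − W12 covers 30 − 12 = 18 weeks, of which 6 are washout and 12 are period-2 treatment. It therefore mixes any fading of the period-1 effect, and any drift during the washout, with the period-2 response.

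**The case against.** The strongest reply is that the text already requires the week-18 scan. The trial is single-centre, and nothing in the protocol says that the table overrides the text. If the text was followed, no data are lost and only the table needs correcting. This stands, and it makes the consequence conditional.

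Several stronger readings are tempting, and the document does not support them:

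- *Steatosis as a whole lacks a period-2 baseline.* It does not. Arginase, prolidase and RBP-4 are named as steatosis markers in the Secondary outcomes section, and Table 1 schedules steatosis markers at W18. The main objective is worded in terms of biomarkers, so it is not left without a baseline either. Only ultrasound grade is affected.
- *The treatment effect on ultrasound grade cannot be estimated.* It can. Both schedules contain W12 and W30, so each participant's end-of-period grades can be contrasted between probiotic and placebo, provided carryover is negligible.
- *The ultrasound result will be biased by a calculable amount.* That would follow only from an analysis that takes week 12 as the period-2 baseline, and no section plans one. It would also need an additive effect, which is doubtful for a graded finding.
- *The food frequency questionnaire rows conflict too.* The text says that "subjects will complete the Food Frequency Questionnaire (FFQ) at the beginning of each intervention period", and Table 1 adds W12 and W30. The text does not say that it is completed only at the beginning, so the extra time points are not a clear contradiction.

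**Conclusion.** The inconsistency is real, and it is not an artefact of how the table was read. If Table 1 is followed, ultrasound-graded steatosis loses one of four scans and one of two within-period changes per participant. The period-2 change, the planned start-to-finish comparison for period 2 and a direct check of return to baseline after washout are then not available for this measure. If the text is followed, nothing is lost beyond a correct table. The protocol article does not show which schedule is in use.

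The matter deserves correction because hepatic steatosis is a listed secondary outcome and ultrasound is the stated means of grading it. It does not touch the primary outcome: plasma LPS is marked at W0, W12, W18 and W30. The missing midpoint dietary record and IPAQ are a separate mismatch of the same kind.

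**What to change.** 1. Mark hepatic ultrasound at V5 (W18) in Table 1, so that it agrees with the Outcome measures section. Against the text this costs nothing, because the scan is already promised. Against Table 1 as drawn, it is one more scan per participant, at most 60.
2. The Trial status section says that the trial is ongoing, so some week-18 visits may already have passed. For any participant whose week-18 scan was missed, state in advance that the end-of-period ultrasound grades (W12 and W30) are used and that week 12 is not taken as the period-2 baseline. This costs a sentence.
3. Reconcile the 3-day dietary record and IPAQ rows of Table 1 with the section on dietary and physical activity control, which asks for both at the midpoint of each period. This is an edit to the table or to the text, depending on which schedule was intended.

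No change to the food frequency questionnaire row is needed on this account.

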#### Primary outcome

The primary outcome will be the change in plasma lipopolysaccharide (LPS) concentration. The determination of LPS concentration and LPS-binding lipoprotein (LBP) will be performed by a simple ELISA (Cloud-Clone Corp., Houston, USA).

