### Statistical analysis

Data analyses will be performed at the end of the intervention, therefore, a replacement or substitution of a withdrawal subject is not planned; therefore, the missing data will be considered unavailable data.

The normality of variables will be assessed. Variables not following a normal distribution will be transformed. Normal variables will be expressed as the mean and standard error of the mean. An intention-to-treat analysis will be performed for the analysis of efficacy. In order to determine differences in basal characteristics, a paired *t-test* will be used. Carryover effects will be assessed by three-way ANOVA. A general lineal model for repeated measurements will be performed to evaluate differences between variables at the beginning, midpoint, and end of each intervention period. Two-way ANOVA will be used to determine the influence of treatment (probiotic or placebo) and time on the continuous dependent variables. Statistical analyses will be performed using IBM SPSS statistics v22.

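### The LPS change outcome with covariate-free ANOVA amounts to an unadjusted change-score comparison, costing 0 to 50% of the precision that adjusting for the t0 and t18 values would give

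*Protocol article*

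**What the plan says.** The Primary outcome section states: "The primary outcome will be the change in plasma lipopolysaccharide (LPS) concentration". The Abstract (Methods/design) adds the time point, "The primary outcome will be the change in plasma lipopolysaccharide (LPS) levels at 12 weeks", and the model: "a mixed ANOVA model will be employed to calculate changes in the outcome variables".

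The Statistical analysis section lists two further models. One is for the course over visits: "A general lineal model for repeated measurements will be performed to evaluate differences between variables at the beginning, midpoint, and end of each intervention period". The other is for the treatment comparison: "Two-way ANOVA will be used to determine the influence of treatment (probiotic or placebo) and time on the continuous dependent variables". Neither has a baseline covariate, and no model is named as the primary one. Baseline values appear only in a test: "In order to determine differences in basal characteristics, a paired" t-test is to be used.

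Under Outcome measures, blood is drawn "at the beginning and at the end of each intervention period (t0, t12, t18 and t30"). Table 1 shows plasma LPS at those same four visits and not at the midpoint visits. Each completer therefore contributes two period baselines (t0, t18) and two end-of-period values (t12, t30).

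**The concern.** In a crossover the treatment contrast is already within-person, so stable differences between people cancel without any baseline. Subtracting each period's baseline brings in the measurement and biological noise of two more LPS values. That subtraction pays only to the extent that the baseline difference between periods predicts the end-of-period difference. A change score fixes the baseline coefficient at 1 whatever the data show. A covariate lets the data set it.

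At stake is the precision of the primary comparison in a small trial. The plan has a minimum of 21 per arm and 60 recruited, replaces no withdrawals, and counts compliance of 80% or less, pregnancy and new diabetes as dropouts. Samples already scheduled could yield a tighter estimate than the stated analysis takes from them.

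**Working it through.** **The plan's own figure.** The Sample size section gives 21 per arm at 80% power and 5% significance but no difference, SD or correlation, so it cannot be reproduced. Solving backwards (two-sided, 1.960 + 0.842 = 2.802):

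- as a two-group comparison, 2.802 × √(2/21) = 0.865 SD;
- as 42 crossover completers, 2.802/√42 = 0.432 SD of the within-person contrast.

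Nothing in the section ties the figure to change scores.

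**Why the listed models reduce to a change score.** With a starting and a final value per period, the treatment-by-time term asks whether the start-to-end change differs between probiotic and placebo.

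**Variances.** For each participant let E = t12 − t30 and B = t0 − t18, each with variance V, and let r be their correlation within sequence.

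- Change-score contrast: Var(E − B) = 2V(1 − r).
- E adjusted for B: V(1 − r²).
- Ratio, change score to adjusted: 2(1 − r)/(1 − r²) = 2/(1 + r).

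The share of precision lost is 1 − (1 + r)/2 = (1 − r)/2.

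**The treatment main effect is no way out.** It averages starting and final values, so rescaled to the same effect it rests on E + B, with variance 2V(1 + r). Its efficiency relative to adjustment is (1 − r)/2, at most one half for r ≥ 0.

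**Size over assumed r.** Suppose 42 completers give exactly 80% power on change scores. Power with adjustment is then Φ(2.802/√((1 + r)/2) − 1.960).

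| r (assumed) | Adjusted ÷ change-score variance | Power with adjustment | Completers needed instead of 42 |
|---|---|---|---|
| 0 | 0.50 | 97.7% | 21 |
| 0.2 | 0.60 | 95.1% | 26 |
| 0.4 | 0.70 | 91.8% | 30 |
| 0.5 | 0.75 | 89.9% | 32 |
| 0.8 | 0.90 | 84.0% | 38 |
| 1 | 1.00 | 80.0% | 42 |

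r = 0 arises when all four LPS values are equally correlated. A correlation that decays with time over weeks 0, 12, 18 and 30, with a 12-week correlation from 0.3 to 0.9, gives variance ratios of 0.50 to 0.64.

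**Simulation** (42 completers, 8,000 runs per setting, no carryover), change score against adjusted:

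- all correlations 0.6: 78.3% against 96.6%;
- within-period 0.7, others 0.5: 77.8% against 89.6%;
- within-period 0.8, others 0.4: 77.3% against 83.5%.

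The change-score figures fall just below 80% because the tests use the t distribution. Both estimators were unbiased.

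**If carryover is present.** Let a first-period probiotic effect c persist in those who took probiotic first.

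- Equal at t18 and t30: E and B both shift by −c in that sequence. The change-score bias is 0; the adjusted bias is −(1 − r)c/2. With c = 0.4 SD this is −0.20 at r = 0 and −0.12 at r = 0.4.
- Present at t18, gone by t30: only B shifts. The change-score bias is +c/2 = 0.20; the adjusted bias is rc/2, or 0 at r = 0 and 0.08 at r = 0.4.

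**The case against.** The strongest objection is that adjustment is not free. The washout is six weeks and the plan itself intends to assess carryover. If a first-period effect persists equally at t18 and t30, the change score cancels it and the adjusted estimate does not, least of all at r = 0, where the precision gain is largest. That stands, so the change score cannot be said to have no benefit. But the argument runs both ways: if the effect has faded by t30, the change score is the more biased. The article does not say which pattern is expected, and it relies on the washout and a separate carryover assessment.

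A second objection is that covariates are often left to an analysis plan that is not shown here. The article, however, does more than stay silent: it fixes a change outcome and names models without covariates. It is true that no model is designated as primary, so the change-score reading is inferred from the outcome definition and the list of models.

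Some stronger readings are tempting and are not supported:

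- *Half the information is lost, or power would rise from 80% to about 98%.* That is the r = 0 case under an assumed calibration. No LPS correlations are given.
- *The changes are analysed on the raw scale.* The plan transforms non-normal variables; the comparison is unadjusted, not necessarily raw.
- *The paired t-test is an error.* The article does not say what it compares. A within-person comparison of t0 with t18 is properly paired. Only a comparison of the two sequences at t0, which are different people, could not be.

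**Conclusion.** The point holds as one of precision. The stated outcome and models lead to an unadjusted change-score comparison, which gives up (1 − r)/2 of the available precision: 50% at r = 0, 25% at r = 0.5, 10% at r = 0.8, none at r = 1. This assumes equal variances for the two within-person differences, r not negative and no carryover. Where in that range LPS falls cannot be told from the article, and the power figures rest on the further assumption that 42 completers give 80% on change scores.

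A reader might infer that the planned analysis is invalid. It is not: without carryover the change score is unbiased, and the choice does not inflate type I error. On the baseline test, all that remains is that pairing cannot serve for a sequence comparison at t0, and that testing baselines does not replace adjusting for them.

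**What to change.** Before unblinding, state one primary estimate: the probiotic–placebo difference in end-of-period LPS (t12 and t30, transformed if the plan's normality rule calls for it). Take it from the crossover mixed model with sequence, period and treatment. Add two covariates: the participant's mean of the t0 and t18 values, and each period baseline's deviation from that mean. Report mean change by treatment descriptively, and keep the change-score comparison as a sensitivity analysis, since the two respond differently to persisting first-period effects. Say what the paired t-test compares, and do not use it between sequences at t0.

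The cost is a change of analysis wording and about two degrees of freedom. No visits, samples or participants are added. The Trial status section describes the trial as ongoing with analyses continuing, so the change should be dated and made before LPS is seen by treatment.
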